## Abstract

**Background:**

Acute exacerbations (AEs) are key events in the progression of chronic obstructive pulmonary disease (COPD), accelerating the decline in lung function and increasing mortality considerably. Inhaler therapy is essential for COPD management; however, incorrect use of inhalation techniques can reduce drug efficacy and increase AE frequency. To optimize the effectiveness of inhaler use, we aim to conduct a randomized controlled trial, in which short-term visual instructions for inhalation use are provided to hospitalized patients with AE of COPD (AECOPD) to reduce AE frequency and severity within 12 weeks.

**Methods:**

This will be a single-center, randomized controlled trial including hospitalized patients with AECOPD who meet the inclusion criteria at the China–Japan Friendship Hospital. The patients will be randomly assigned to a visual inhaler technique instruction (VIT; experimental) or traditional inhaler technique education (TIE; control) group. During hospitalization, the TIE group will receive two standardized TIE sessions conducted by a respiratory nurse. In contrast, the VIT group will receive two VIT sessions under a physical therapist's supervision. The primary outcome will be AE frequency within 12 weeks after discharge. Secondary outcomes include all-cause mortality and each AE's severity (EXACT-Pro score) over 12 post-discharge weeks. Secondary outcomes will also include lung function, physical fitness (6-min walk test score, grip strength, and maximum voluntary contraction of knee extension), respiratory muscle strength (maximal inspiratory and expiratory pressures), dyspnea severity (modified Medical Research Council scale score), inhaler medication adherence, and quality of life (COPD Assessment Test score) at week 12 after discharge.

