**Questionnaire**						
mMRC				✓		✓
CAT				✓		✓
TAI		✓				✓
EXACT-PRO					✓ (daily)	
Frequency and severity of AE					✓ (weekly)	

PIFr, peak inspiratory flow resistance; EIT, effective inspiratory time; EIV, effective inspiratory volume; IIFSC, integrated inspiratory flow system score; IOCL, inhalation operation chick list; MIP, maximum inspiratory pressure, MEP, maximum expiratory pressure, MVC, maximal voluntary contraction; 6MWT, 6 minutes walking test; mMRC, modified medical research council dyspnea scale; CAT, COPD assessment test; TAI, test of the adherence to inhalers; EXACT-PRO, exacerbation of chronic pulmonary disease tool-patient reported outcome; AE, acute exacerbations.

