#### Secondary outcomes

2.5.2

The following secondary outcomes will be considered.

(1) EXACT-Pro scale score: The EXACT-Pro questionnaire allows patients to self-assess AE-related symptoms, including dyspnea, cough, sputum production, chest symptoms, and quality of life. The scale has good reliability and validity and consists of 14 items. Each item is scored from 0 to 5, with the total score being converted into a 0–100 scale based on logarithmic transformation. The higher the score, the greater the AE severity. We will collect the relevant data once daily over 12 weeks.

(2) AE severity: AE severity will be assessed according to the GOLD 2024 guidelines by using the following grading system: Mild, AE requiring short-acting bronchodilator treatment; Moderate, AE requiring short-acting bronchodilator plus antibiotics and/or oral corticosteroids treatment; and Severe, AE requiring hospitalization or emergency department visit. Based on these definitions and grading standards, a structured interview record form will be created to collect data on AE severity within 12 weeks after discharge. See Appendix 1 for additional details.

(3) All-cause mortality

(4) Inhalation technique assessment: This will be divided into inhalation flow rate evaluation and inhalation operation checklist.

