### Data management and quality control

2.6

Patients will be required to complete the EXACT-Pro questionnaire delivered via a WeChat mini program at 9:30 a.m. daily. Research assistants will check the questionnaire completion status at 7:00 p.m. and remind patients via telephone to complete it promptly. Research assistants will also call patients weekly to inquire about their respiratory symptoms over the past week and provide verbal reminders to take their medication regularly.

To minimize measurement errors, each participant will be assessed by the same evaluator during every visit. Study data will be stored on a password-protected platform and backed up to a secure external hard drive; data access will be restricted only to authorized researchers and staff. Automatic plausibility controls will be implemented during data entry to detect any inconsistencies or inaccuracies.

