### Statistical analysis

2.7

Data analysis will follow the modified intention-to-treat principle to ensure complete randomization, minimize selection bias, and reflect real clinical practice. Missing data will be addressed using multiple imputation to reduce potential bias resulting from missing information, ensuring the robustness and accuracy of the analysis. All statistical tests will be performed according to a preestablished statistical analysis plan. SPSS (version 21.0) will be used for all data analyses, and two-tailed *p* < 0.05 will be considered to indicate statistical significance.

Continuous variables will be expressed as means ± standard deviations or median (Interquartile) where appropriate, and categorical variables as frequencies and percentages. Normality testing for continuous variables will be performed using the Shapiro–Wilk or Kolmogorov–Smirnov test, and homogeneity of variance will be assessed using the Levene test. For continuous variables that are normally distributed with equal variance, intergroup comparisons will be conducted using the independent-samples *t*-test. For continuous variables that do not meet the normality or homogeneity assumptions, the Mann–Whitney *U*-test will be employed. For discrete variables (such as the AE number and severity over 12 weeks), intergroup comparisons will be performed using the chi-square, Fisher exact, or Cochran–Mantel–Haensel χ^2^ test.

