### Sample size calculation

2.8

Our literature review indicated that the AE rate within 3 months after hospitalization for AECOPD is approximately 48.9% (5). Our preliminary data (unpublished) indicate that after VIT, the treatment failure rate at 90 days is approximately 15%. Therefore, the expected effect size between the two groups is about 33.9%. We set the significance level α = 0.05 and the statistical power at 80% (i.e., β = 0.20), with a dropout rate assumed to be 20%. The calculated values for *Z*_α_/2 and *Z*β are 1.96 and 0.84, respectively, with standard deviation σ = 0.614, effect size Δ = 0.339. Based on these parameters and sample size calculations, each group must include ≥32 patients. To ensure data accuracy and account for potential dropouts, we plan to recruit 40 patients per study group, totaling 80 participants.

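### AE severity means the EXACT-Pro score in the abstract but a GOLD treatment grade in the body, and a per-event severity comparison, on either measure, would cover only patients who exacerbated

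*Protocol article*

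**What the plan says.** The places that bear on this, all in the protocol article:

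- **Abstract, Methods:** "Secondary outcomes include all-cause mortality and each AE's severity (EXACT-Pro score) over 12 post-discharge weeks". The GOLD grade is not mentioned in the abstract.
- **Abstract, Background:** lowering both the frequency and the severity of AEs within 12 weeks is the stated aim.
- **Section 2.5.2(1), EXACT-Pro:** a secondary outcome of its own, on a 0–100 scale. "We will collect the relevant data once daily over 12 weeks". Its reading is given as "The higher the score, the greater the AE severity".
- **Section 2.5.2(2), AE severity:** "AE severity will be assessed according to the GOLD 2024 guidelines by using the following grading system". The three levels are set by the treatment or care that the event required.
- **Table 1:** EXACT-PRO is a daily row. "Frequency and severity of AE" is a separate, weekly row.
- **Section 2.6:** "Patients will be required to complete the EXACT-Pro questionnaire delivered via a WeChat mini program at 9:30 a.m. daily". Completion is not tied to having an AE.
- **Section 2.7:** "For discrete variables (such as the AE number and severity over 12 weeks), intergroup comparisons will be performed using the chi-square", with the Fisher exact and Cochran–Mantel–Haenszel tests as alternatives.

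**The concern.** Three different quantities can be meant by AE severity here: a symptom score during events, a symptom score over all 84 follow-up days, and the level of care an event required. They need not agree. A reader of the abstract will expect the first. A reader of section 2.5.2 will expect the third, with the second alongside it under a sentence that also calls it AE severity.

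The abstract's wording has a further consequence. A score attached to each AE exists only for patients who had one. Having an AE is the primary outcome and is expected to depend on the assigned arm, so this subset is not protected by randomization. If VIT mainly prevented mild events, the events left in the VIT arm would look worse than those under TIE even though no patient was harmed. If it mainly prevented severe events, the remaining ones would look milder although VIT had not eased any of them. Either way, a difference in per-event severity could not be read as an effect of VIT on severity.

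**Working it through.** **Which definition each place supports**

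| Place | Measure it fits | Tied to an AE? |
|---|---|---|
| Abstract, Methods | EXACT-Pro | Yes, by its wording |
| 2.5.2(1) | EXACT-Pro, described as AE severity | No; daily for 12 weeks |
| 2.5.2(2) | GOLD grade | Yes, a grade belongs to an event |
| Table 1 | EXACT-Pro and AE severity in separate rows | EXACT-Pro daily; AE row weekly |
| 2.6 | EXACT-Pro | No |
| 2.7 | Categorical severity, so the grade and not a 0–100 score | Not stated |

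The body treats the grade as AE severity in three places (2.5.2(2), Table 1, 2.7). The abstract, and one sentence in 2.5.2(1), say otherwise.

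**How many patients a per-AE comparison would contain**

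The plan gives no figure for any severity outcome, so there is none to reproduce. The inputs come from section 2.8. It states that "the AE rate within 3 months after hospitalization for AECOPD is approximately 48.9" per cent, gives a VIT treatment failure rate at 90 days of 15%, plans 40 patients per group, and assumes 20% dropout, 80% power and normal quantiles of 1.96 and 0.84. Taking the 15% as an AE rate is an assumption, because the section calls it treatment failure.

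- TIE: 0.489 × 40 = 19.6, about 20 patients.
- VIT: 0.15 × 40 = 6 patients.

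**What such a comparison could detect** (one score per patient, equal variances, normal approximation)

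Smallest detectable difference in SD units = (1.96 + 0.84) × √(1/n₁ + 1/n₂).

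- Patients with an AE only: 2.80 × √(1/6 + 1/20) = 1.30 SD.
- All 40 per group: 2.80 × √(2/40) = 0.63 SD.
- After 20% dropout (32 per group): 15.6 and 4.8 patients with an AE, giving 2.80 × √(1/15.6 + 1/4.8) = 1.46 SD, against 2.80 × √(2/32) = 0.70 SD for everyone.

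These figures describe the comparison that the abstract's wording implies. They do not describe an analysis that the body specifies.

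**Size of the selection bias**

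It depends on which events VIT prevents, and the document gives no information on that. It is zero if prevention is unrelated to severity and can take either sign otherwise, so no single figure is offered.

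**The case against.** The strongest reply is that the Methods section is clear enough. It numbers EXACT-Pro and AE severity as two separate secondary outcomes, schedules them separately, and names categorical tests for severity. On this view the abstract has merely compressed two outcomes into one phrase. EXACT-Pro is requested from patients every day without any AE condition, and how 84 daily scores are summarised normally belongs in the analysis plan, which section 2.7 mentions and which is not shown.

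Much of this stands, and it rules out some stronger readings:

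- A reader might infer that the trial as a whole will compare EXACT-Pro only among patients who exacerbated. The document does not support that. Only the abstract's wording implies it.
- A reader might infer that the conditioning problem is peculiar to EXACT-Pro. It is not. A GOLD grade given to each AE also exists only where an AE occurred.
- A reader might infer that the investigators are free to report whichever severity result is favourable. Both measures are listed in advance as separate secondary outcomes, so the fault is an ambiguous label.
- A reader might see the lack of an EXACT-Pro value before follow-up in Table 1 as a flaw. Randomization makes the post-discharge comparison valid without one, and a V0 score would fall within the index exacerbation.

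What the reply does not remove is the contradiction itself. An unseen analysis plan could follow the abstract or section 2.5.2, but it could not make both correct. The body is also not wholly clean, because 2.5.2(1) still interprets EXACT-Pro as AE severity.

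**Conclusion.** The concern holds as an inconsistency between abstract and body over what AE severity means, made worse by one sentence in 2.5.2(1). The primary outcome is unaffected. It should still be corrected, because severity is part of the stated aim and the abstract's version would not be a randomized comparison.

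If the abstract's wording were followed, about 6 VIT and 20 TIE patients would be compared, and the smallest detectable difference would be about 1.30 SD instead of 0.63 SD with all 40 per group. This rests on reading the 15% failure rate as an AE rate, one score per patient and no dropout; with 20% dropout the figures are 1.46 and 0.70 SD. Bias from the selected subset is possible in either direction, and its size cannot be derived from the document. The same caution applies to any per-event comparison of GOLD grades.

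**What to change.** 1. Reserve the term AE severity for the grade in section 2.5.2(2). Compare it per patient in all randomized patients, for example as the worst grade over 12 weeks with no AE as the lowest category. The categorical tests named in section 2.7 can be applied to such a variable.
2. Define the EXACT-Pro outcome as a patient-level summary of the daily scores over the 12 weeks, such as the mean, in all randomized patients whether or not they had an AE. Section 2.7 plans a modified intention-to-treat analysis; membership of that set should not depend on having had an AE.
3. Report EXACT-Pro scores during AEs as descriptive only.
4. Correct the secondary-outcome sentence in the abstract, and reword the sentence in 2.5.2(1) that equates a higher score with greater AE severity.

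The cost is wording. The daily scores and weekly AE records are already planned for collection, so no visit or questionnaire is added. The analysis plan must say how deaths and withdrawals enter both patient-level outcomes. The real downside is that EXACT-Pro then measures average symptom burden and not the peak severity of events, which would be available only descriptively.

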**Discussion:**

We aim to address the issues related to inhaler technique education that are often overlooked in clinical practice. Our findings may provide evidence for clinical practice and enable further optimization of inhaler technique education management strategies for patients with AECOPD.

## Background

1

Chronic obstructive pulmonary disease (COPD) is a progressive disorder characterized by persistent inflammation of the airways, alveoli, and microvasculature, primarily manifested by irreversible airflow limitation (1). Acute exacerbations (AEs) are major negative events occurring in the course of COPD. Clinical observations have demonstrated that patients experiencing frequent AEs of COPD (AECOPD) have a significantly faster decline in lung function indicators, such as forced expiratory volume in 1 s (FEV1) and peak expiratory flow (PEF), compared to those with a stable disease (2). After the occurrence of an AE requiring hospitalization, the risk of mortality in the short term increases significantly (3, 4). Even after remission, patients with AECOPD have a high recurrence risk. In patients with AECOPD, the rate of AE recurrence within 90 postdischarge days can be as high as 48.9% (5). The more frequent the recurrences, the higher the mortality rate (4). Therefore, reducing AE recurrence is essential for improving the quality of life and reducing mortality, healthcare visit frequency, and medical costs among affected patients with COPD (6, 7). According to the 2024 report of the Global Initiative for Chronic Obstructive Lung Disease (GOLD), inhaler therapy is the preferred treatment for stable COPD patients, and correct use of inhaled medications can reduce the mortality risk in patients with a history of frequent AEs, severe AEs, or both significantly (8, 9).

During inhalation therapy, the drug delivery and deposition process involves the medication traveling through the oral cavity and pharynx, followed by its entry into the trachea, bronchi, and small airways, and ultimately its arrival and deposition into the alveoli and small airways. Here, the patient's mastery of the correct inhalation technique mainly influences the effectiveness of drug delivery and deposition. In particular, this effectiveness is closely related to not only the appropriate maintenance of inspiratory flow rate but also the proper execution of inhalation techniques.

Numerous studies have confirmed that an improper inspiratory flow rate—too low or too high—can hinder drug delivery (3, 10). The most commonly used parameter for assessing the inhalation technique is peak inspiratory flow rate (PIFr); it is the maximum flow rate generated by a patient during inhalation to overcome the internal resistance of an inhaler (6). Different types of inhalers, such as pressurized metered dose inhaler (pMDI), dry powder inhaler (DPI), and soft mist inhaler (SMI), have varying PIFr requirements because of varied drug particle release mechanisms and device resistance. The optimal inspiratory flow rate for DPIs is approximately 60 L/min, which generates turbulence inside the device, facilitating the dispersion of the powder into fine particles that can be carried into the airways via airflow (11). In contrast, pMDIs and SMIs do not rely on the patient's active inhalation to generate turbulence for drug particle release and thus have an optimal inspiratory flow rate of about 30 L/min (12). If a patient's measured PIFr is suboptimal, it may limit medication delivery to the lower airways, thereby reducing efficacy (13). In addition to inspiratory flow rate, proper inhalation techniques are crucial for drug deposition. Adequate exhalation before inhalation minimizes residual volume, increasing the volume of medicated air inhaled and enhancing drug delivery to small airways. Furthermore, prolonging breath-holding after inhalation facilitates the deposition of fine drug particles in small airways via Brownian motion, reducing the proportion of exhaled suspended particles (14).

Many recent studies have considered inspiratory flow rate to be an independent evaluation parameter. However, inhaler device preparation, exhalation before inhalation, and breath-holding after inhalation are the main components of the inhalation technique, which are crucial for assessing the completeness and effectiveness of drug delivery. Most studies have primarily focused on individualized inhalation flow rate guidance based on PIFr measurements; however, studies combining PIFr assessment with a comprehensive inhalation technique training remain limited. Despite the importance of using the correct inhalation technique, inhaler technique education remains insufficient. According to the 2024 GOLD guidelines, physicians must combine explanation and demonstration to ensure understanding among their patients and verify their mastery of the technique by encouraging them to perform it onsite. However, 36%−67% of physicians cannot fully or accurately describe or master the key steps of inhaler device use (15). Moreover, research evaluating inhaler devices and training tools remains scant (16–18). In summary, inhalation technique evaluation and education can be considerably challenging and warrant improvement.

We therefore plan to conduct a randomized controlled trial comparing the effects of short-term visual inhaler technique instruction (VIT) and traditional inhaler technique education (TIE) before discharge in hospitalized patients with AECOPD. In particular, we will assess how the two interventions affect the rate of AEs within 12 weeks after discharge. Our objective is to collect data and establish clinical pathways for inhalation technique assessment and education.

## Methods and analysis

2

### Study design

2.1

This will be a single-center, prospective, and parallel randomized controlled trial. Participants will be randomly assigned to a VIT or TIE group for corresponding interventions and follow-up. The study period will begin 1 week before discharge and include a 12-week follow-up after discharge. Outcomes will be measured at baseline (V0), after instruction (V1), before discharge (V2), and at week 12 after discharge (V3).

This trial is registered at ClinicalTrials.gov (registration number: ChiCRT2500097816) on 26/02/2025. The study protocol is reported according to the Standard Protocol Items: Recommendations for Intervention Trials 2013 (19) guidelines, and the intervention procedures are described according to the Consolidated Standards of Reporting Trials (CONSORT) 2025 Checklists. Figure 1 illustrates the CONSORT flow diagram for this study, and Table 1 summarizes the study schedule and assessments.

**Figure 1 F1:**
[figure not shown]
Technical flowchart of the present study.

**Table 1 T1:** Summary of study schedule.

**Schedule of assessments and measurements across study time points**	**Enrollment**	**Baseline (V0)**	**After instruction (V1)**	**Before discharge (V2)**	**Follow-up**	**At week 12 post-discharge (V3)**
**Eligibility screening**						
Informed consent	✓					
Randomization		✓				
Allocation		✓				
**Interventions**						
VIT group		✓				
TIE group		✓				
**Inhalation technique assessment**						
PIFr		✓	✓			✓
EIT		✓	✓			✓
EIV		✓	✓			✓
IIFSs:		✓	✓			✓
IOCL		✓	✓			✓
**Pulmonary function**						
FVC & FVC%				✓		✓
FEV1 & FEV1%				✓		✓
FEV1/FVC				✓		✓
**Respiratory muscle strength assessment**						
MIP				✓		✓
MEP				✓		✓
**Assessment of physical function**						
Grip strength				✓		✓
MVC of Knee extension				✓		✓
6MWT				✓		✓
**Questionnaire**						
mMRC				✓		✓
CAT				✓		✓
TAI		✓				✓
EXACT-PRO					✓ (daily)	
Frequency and severity of AE					✓ (weekly)	

PIFr, peak inspiratory flow resistance; EIT, effective inspiratory time; EIV, effective inspiratory volume; IIFSC, integrated inspiratory flow system score; IOCL, inhalation operation chick list; MIP, maximum inspiratory pressure, MEP, maximum expiratory pressure, MVC, maximal voluntary contraction; 6MWT, 6 minutes walking test; mMRC, modified medical research council dyspnea scale; CAT, COPD assessment test; TAI, test of the adherence to inhalers; EXACT-PRO, exacerbation of chronic pulmonary disease tool-patient reported outcome; AE, acute exacerbations.

### Study population and recruitment

2.2

All patients will undergo initial screening by physicians in the Department of Respiratory and Critical Care Medicine to confirm AECOPD diagnoses. Independent researchers will then conduct a secondary screening according to inclusion and exclusion criteria (Table 2) to ensure that only eligible patients are included. Patients or their legal guardians will be required to provide informed consent to participate.

**Table 2 T2:** Inclusion, exclusion, and withdrawal criteria.

**Inclusion criteria**	**Exclusion criteria**	**Withdrawal criteria**
(1) A previous pulmonary function test confirming a COPD diagnosis (postbronchodilator FEV1/FVC < 0.7) and currently hospitalization due to AECOPD	(1) Severe cognitive impairment; inability to understand assessments or instructions; and inability to comprehend the study's nature, scope, and potential consequences	(1) Hospitalization and receipt of treatment for non-AECOPD pulmonary diseases (e.g., lung volume reduction surgery, severe chest trauma) within 12 weeks after discharge
(2) Age = 40–85 years	(2) Bronchiectasis as the primary COPD manifestation	(2) Voluntary request to withdraw from the intervention or terminate follow-up observations
(3) Hospitalized patients with AECOPD who no longer meet GOLD 2025 criteria for respiratory failure or ventilatory failure.	(3) Complication due to malignancy	
(4) Continual, regular use of a fixed bronchodilator inhaler for >3 months after discharge	(4) A history of lung volume reduction surgery within 3 months before admission;	
(5) Use of an Ellipta, pMDI, or soft mist inhaler (SMI) as the inhalation device	(5) Severe diseases, such as heart, liver, kidney diseases, or hemodynamic instability	
(6) Provision of written informed consent	(6) Currently pregnant, breastfeeding, or planning to become pregnant during the study	

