### Randomization, allocation concealment, and blinding

2.3

All patients will be randomly allocated at a 1:1 ratio to either the VIT or TIE group by using a random number table generated by an independent statistical analyst with SPSS. In accordance with the 2025 WHO age classification, participants will be stratified into two age groups (40–65 years and 66–85 years) before randomization to ensure balanced distribution across intervention arms. The assignment details will then be sealed in opaque envelopes. After each participant provides written informed consent and completes their baseline assessments, the study coordinator will open the envelope to reveal the participant's group allocation.

Because of the nature of the intervention, neither the participants nor the instructors will be blinded; nevertheless, the outcome assessors and statistical analysts will remain blinded to group assignments.

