### Interventions

2.4

All patients will receive two inhaler usage instruction sessions during hospitalization and will be followed up weekly via telephone over 12 weeks after discharge. Researchers blinded to the group assignments will implement this measure. It will ensure regular use of inhalation medications in both groups during the study period and enable recording of any possible AE events and their severity.

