#### Primary outcome

2.5.1

The primary outcome of this study will be AE frequency within 12 weeks after discharge, which will be monitored weekly via telephone.

The GOLD 2024 guidelines define AECOPD as a sudden worsening of respiratory symptoms, with dyspnea as the primary symptom. Secondary symptoms may include increased sputum volume and thickness, aggravated coughing, and wheezing. During this study's weekly follow-ups, an AE will be recorded if the patient experiences a significant worsening of dyspnea (primary symptom) lasting for ≥2 days or if two or more secondary symptoms worsen beyond normal daily variation over ≥2 days. The duration of each exacerbation will be carefully documented to prevent record duplication during subsequent follow-ups. A structured interview and record form will be developed to capture data on the number of AECOPD exacerbations over 12 weeks after discharge. See Appendix 1 for additional details.

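### Table 2 withdraws randomized patients within the outcome window without saying that follow-up continues, and a modified intention-to-treat set cannot by itself preserve the full randomized comparison

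*Protocol article*

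**What the plan says.** Table 2 (section 2.2) has two withdrawal criteria. The first is "Hospitalization and receipt of treatment for non-AECOPD pulmonary diseases (e.g., lung volume reduction surgery, severe chest trauma) within 12 weeks after discharge". The second is "Voluntary request to withdraw from the intervention or terminate follow-up observations".

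Both act after randomization. Section 2.3 places allocation in hospital: "After each participant provides written informed consent and completes their baseline assessments, the study coordinator will open the envelope". The intervention is brief and precedes follow-up (section 2.4): "All patients will receive two inhaler usage instruction sessions during hospitalization and will be followed up weekly via telephone over 12 weeks after discharge". The primary outcome (section 2.5.1) covers the same 12 weeks as the first criterion: "The primary outcome of this study will be AE frequency within 12 weeks after discharge, which will be monitored weekly via telephone". All-cause mortality over those weeks is a secondary outcome (Abstract; section 2.5.2).

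On analysis, section 2.7 states: "Data analysis will follow the modified intention-to-treat principle to ensure complete randomization, minimize selection bias, and reflect real clinical practice". It continues: "Missing data will be addressed using multiple imputation to reduce potential bias resulting from missing information". The article does not define the modification. It refers to a pre-established analysis plan, which is not shown.

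**The concern.** A patient admitted for another lung disease in week 5, say, is still at risk of an exacerbation and of death until week 12. Withdrawing that patient gives up information the trial is already set up to collect. The admission may also carry information about risk. The primary event is defined by symptoms (worse dyspnoea, or at least two secondary symptoms, for two days or more), and some other lung diseases present in the same way. Labelling an admission AECOPD or not can then decide between a counted event and a withdrawal.

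The second criterion raises a related problem. The intervention is two sessions before discharge, and the outcome comes from telephone calls afterwards. Declining a session gives no reason to stop the calls, yet the wording makes it the same kind of withdrawal as refusing follow-up.

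At stake are exacerbation frequency and mortality, and whether the comparison remains one between the groups as randomized. The rationale in section 2.7 does not settle this, because the word *modified* signals that some randomized patients may be left out.

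**Working it through.** **Inputs (section 2.8).** Control rate p1 = 0.489; VIT rate p2 = 0.15; difference 0.339; σ = 0.614; Z values 1.96 and 0.84; dropout 20%; at least 32 per group required, 40 recruited.

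**The plan's own figure.** σ equals √[p1(1−p1) + p2(1−p2)] = √(0.2499 + 0.1275) = 0.614. Then n = (1.96 + 0.84)² × 0.614² / 0.339² = 25.7 per group. Dividing by 0.8 gives 32.1, which agrees with the stated 32, and 32/0.8 = 40. So 40 per arm randomized and 8 per arm lost is the plan's own scenario.

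**How far lost outcomes could move the difference.** The documents give no withdrawal rate by reason, so this is an illustration. It uses the proportion with an exacerbation, the scale of the sample size calculation. Let k of 40 patients per arm have no known outcome, and let the rest follow the planned rates. The observed part contributes 0.339 × (40−k)/40. The unknown part contributes at most k/40 either way (all events in one arm and none in the other). Bounds = 0.339 × (40−k)/40 ± k/40:

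| k per arm | Observed part | ± | Control minus VIT |
|---|---|---|---|
| 1 | 0.3305 | 0.025 | 0.306 to 0.356 |
| 2 | 0.3221 | 0.050 | 0.272 to 0.372 |
| 4 | 0.3051 | 0.100 | 0.205 to 0.405 |
| 8 | 0.2712 | 0.200 | 0.071 to 0.471 |

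For mortality there is no planning rate. Each patient with unknown vital status can move that arm's proportion by up to 1/40 = 2.5 points.

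**When loss produces bias.** Suppose no true effect, 48.9% in both arms, a fraction w withdrawn with event risk r, and analysis of the remainder without imputation. The observed rate is (0.489 − w·r)/(1 − w).

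- Equal w and equal r in both arms: spurious difference 0.
- 10% lost in one arm, none in the other: 0 points if r = 48.9%; 2.3 if r = 70% (0.419/0.9 = 0.466); 4.6 if r = 90% (0.399/0.9 = 0.443).
- 20% against 10%: 0, 2.9 and 5.7 points for the same three risks.

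The arm that loses more high-risk patients looks better. Bias in this example needs withdrawal that is both related to outcome and unequal between arms.

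**Power.** At 48.9% against 15%, power is 91.7% with 40 per arm and 84.6% with 32. Power is not the issue.

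**The case against.** A reader might infer that withdrawn patients are dropped from the primary and mortality analyses for outcome-related reasons. The document does not say this. Table 2 does not state that their data are discarded or that they leave the analysis set. Section 2.7 plans multiple imputation, which points away from simple deletion. The definition of the modified set may stand in the unseen analysis plan, so its absence from an article is no fault. An AECOPD admission does not trigger withdrawal, and the two examples given, surgery and chest trauma, are easily told from an exacerbation. That withdrawal removes the sickest patients is therefore an inference. Although participants know their group, outcome assessors and the weekly callers are blinded (sections 2.3 and 2.4), which limits differential labelling.

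A reader might also infer that a handful of withdrawals would decide the trial. That depends on the table chosen. With 13/32 against 5/32, p = 0.026 (chi-square) and 0.04999 (Fisher); adding three VIT patients, all with events (8/35), gives 0.117 and 0.187. Near the planned rates, 16/32 against 5/32 gives 0.003 and 0.007, and the same one-sided addition still leaves 0.021 and 0.025.

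All of this stands and limits the point, but it does not remove it. The surgery and trauma are only examples; the rule covers every non-AECOPD lung disease. Imputation replaces obtainable outcomes with modelled ones, normally assuming they are missing at random, which is doubtful when a lung admission causes the loss. It cannot help patients outside the analysis set, and no analysis plan can recover outcomes that were never collected.

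**Conclusion.** The point holds as a weakness in the withdrawal rules and in the stated rationale for the analysis set. It is not proof that patients are excluded from the analyses. The plan allows avoidable loss of exacerbation and vital-status data after randomization, and the claim that a modified set will secure complete randomization is unsupported.

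The size depends on how many are lost. One or two per arm leave the planned 33.9-point difference between 30.6 and 35.6, or between 27.2 and 37.2 points. At the assumed 20% loss the bounds widen to 7.1 and 47.1. These are extreme-case limits on a yes/no outcome at the planned rates, with equal numbers lost in each arm; they do not predict the bias. If losses come only from a few non-AECOPD admissions, the effect is small. The correction is needed before follow-up ends.

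**What to change.** In Table 2, state that a non-AECOPD pulmonary hospitalization is recorded and that exacerbation and vital-status follow-up continues to week 12. Split the second criterion in two: stopping the intervention, after which follow-up continues, and withdrawing consent to follow-up.

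In section 2.7, make all randomized patients, as allocated, the primary analysis set. Use multiple imputation only for outcomes that remain missing, and add a sensitivity analysis censoring at non-AECOPD hospitalization. If a modified set is kept, state its exclusions and remove the claim about complete randomization.

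The cost is small: wording changes and a few extra calls within the existing weekly schedule.
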